### Main and Secondary Objectives

Main Objectives:To evaluate whether our proposed cardio-pulmonary rehabilitation program improves respiratory function and exercise capacity.To compare outcomes between the hospital-based rehabilitation group and the home-based rehabilitation group.

Secondary Objectives:To identify whether this specific CRP achieves higher adherence rates compared to other programs reported in the literature.To determine if adverse effects occur during or after completing the program.To verify whether the program has been conducted in a safe environment and assess its feasibility in natural settings.To determine if the program leads to improvements in the quality of life of these children and their families.

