## 2. Materials and Methods

A parallel randomized controlled trial with a simple assignment has been designed (1:1) to test the effect of a 12-week specific CRP on respiratory function in pediatric patients with intervened CHDs. The trial will be conducted at the Teresa Herrera Maternal and Child Hospital of the University Hospital Complex of A Coruña (CHUAC) and follow the Consolidated Standards of Reporting Trials (CONSORT) Statement [20]; the treatment protocol is described in accordance with the recommendations of SPIRIT [21].

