### 2.4. Sample Size

Since no information has been found on the magnitude of the effect on the topic studied, an effect size of 0.8 has been set, taking into account the scale proposed by Cohen and meta-analysis on the effect of rehabilitation in other respiratory conditions [37]. Sample size calculation was performed for a mean difference analysis of independent groups. The effect size was d = 0.8 alpha level of 0.05, power 80%. The estimated sample size was 26 subjects per group. Considering losses of 10%, the number of subjects needed was 56 subjects. G*Power 3.1 software was used to calculate the sample size.

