### 2.6. Data Analysis

The normality of the data distribution was analyzed with the test of Kolmogorov–Smirnov. For the descriptive analysis, the mean and standard deviation were used if the distribution of the variables was normal; otherwise, the median and interquartile range were calculated. The qualitative variables of the study will be defined by frequencies and percentages.

Student’s *t* test will be used to compare the intergroup means if the distribution of the variables is normal. The non-parametric Mann–Whitney U test will be applied if the normality of the data is not fulfilled. Levene’s test will be used to test the equality of variances between groups. Welch’s *t*-test will be used if the assumption is not met. Repeated measures t-test or the non-parametric Wilcoxon t-test will be applied for the comparison of intragroup means depending on the normality of the data. The Chi-Square test will be used to test the association between categorical variables.

A confidence level of 95% will be considered for the calculation of the confidence intervals and a significance level of 5% for the statistical tests. The statistical program IBM SPSS Statistics version 28.0.1 will be used to analyze the data.

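### No primary variable is named among nine main measures; the 5% level and 80% power describe one unnamed comparison, so the main conclusion could carry a false-positive risk well above 5%

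*Protocol article*

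**What the plan says.** - **Main and Secondary Objectives.** The first main objective is "To evaluate whether our proposed cardio-pulmonary rehabilitation program improves respiratory function and exercise capacity". The second compares the hospital-based and home-based arms on outcomes that it does not specify. Quality of life is secondary.
- **Section 2, Materials and Methods.** The design sentence says the trial was set up "to test the effect of a 12-week specific CRP on respiratory function in pediatric patients with intervened CHDs". Exercise capacity is not mentioned there.
- **Abstract, Outcomes and Table 2.** Lung function is FVC, FEV1, PEF, FEV1/FVC, FEF25%, FEF50%, FEF75% and FEF25–75%. Exercise capacity is oxygen consumption on the treadmill test, given in the abstract as peak VO2. No variable is marked as primary.
- **Section 2.4, Sample Size.** "Sample size calculation was performed for a mean difference analysis of independent groups". "The effect size was d = 0.8 alpha level of 0.05, power 80" (per cent). "The estimated sample size was 26 subjects per group". No outcome is named.
- **Section 2.6, Data Analysis.** Between-group and within-group tests are planned, with "a significance level of 5% for the statistical tests". The section gives no order among the variables.

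**The concern.** A 5% error rate and 80% power are properties of a defined test. The plan reports both as though there were one test, yet its main objective spans two domains and nine continuous measures, and nothing says which of them decides the result.

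As written, one significant spirometry index out of eight, or peak VO2 alone, could be reported as meeting the main objective. The emphasis could also move between lung function and exercise capacity after the results are known, because the objectives and the design sentence do not have the same scope. The stated 5% would then not describe the risk of a false main conclusion.

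**Working it through.** **1. Reproduce the sample size.** Inputs from Section 2.4: d = 0.8, alpha 0.05, power 80%, two independent groups. The article does not state sidedness; two-sided is assumed because it reproduces the stated figure.

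For a t-test with n per group, the noncentrality is d × √(n/2), on 2n − 2 degrees of freedom.

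- n = 26: 0.8 × √13 = 2.88, power 80.7%.
- n = 25: power 79.1%.
- The exact solution is 25.52, so 26 per group, as stated. A one-sided test would need 21.

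So 26 per group is correct for one two-sided test at 5%.

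**2. Count the main measures.** Eight spirometry indices + peak VO2 = 9. Not counted: ventilatory pattern, quality of life (a secondary objective) and within-group tests. Within-group tests in two arms would add 9 × 2 = 18.

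**3. Chance of at least one false positive in nine between-arm tests at 5%, with no true difference.**

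Under independence: 1 − 0.95^9 = 1 − 0.630 = 0.370.

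The indices are correlated, and the article gives no correlations. The figures below come from simulating nine two-sided t-tests with 26 per arm (40,000 replicates). All correlations are assumed.

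| Common correlation | At least one false positive |
|---|---|
| 0 | 36.7% (formula 37.0%) |
| 0.3 | 32.9% |
| 0.5 | 27.6% |
| 0.7 | 20.4% |
| 0.8 | 16.8% |
| 0.9 | 12.9% |
| 0.95 | 9.8% |

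If peak VO2 correlates only 0.3 with each spirometry index, and the eight indices correlate 0.5, 0.7, 0.8 or 0.9 with one another, the figures are 27.9%, 22.8%, 19.7% and 16.1%.

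Relative to 5%: 12.9/5 = 2.6 times at correlation 0.9, 27.6/5 = 5.5 times at 0.5, and 37.0/5 = 7.4 times at the bound.

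**4. What each remedy does to power at d = 0.8.**

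- One named primary at 5%: 80.7% with 26 per group.
- Two variables at 0.05/2 = 0.025 each: 31 per group for 80%.
- All nine at 0.05/9 = 0.0056 each: about 50% per test with 26 per group; 43 per group (86 completers) for 80%.

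**The case against.** **Adjustment can be left to an analysis plan.** This stands. The article condenses a fuller protocol, a 5% level with 95% intervals is standard wording, and silence on adjustment or testing order is not in itself a fault. The choice of variable that sizes the trial is different. Section 2.4 gives effect size, alpha, power, number and software, but not the outcome.

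**Nine main outcomes is an inference.** Partly right. The objectives name two domains, and no sentence declares each index a main outcome or says that any one suffices. The inflation is therefore conditional on that use, which the text leaves open. The strict alternative, that both domains must succeed, would not inflate alpha but would lower power. With one test per domain at d = 0.8, power would be about 0.807 × 0.807 = 65% if the two tests were independent, rising to 80.7% only if they always agreed. Either way, the stated 5% and 80% are not pinned to the main conclusion.

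**Stronger readings that the article does not support.**

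- A reader might infer that the objectives and the design sentence contradict each other. The design sentence omits exercise capacity; it does not say lung function alone. This is incomplete wording.
- A reader might take 37% as the error rate. It needs independence, which is impossible here: FEV1/FVC is computed from two of the other indices, and the flow indices come from the same forced manoeuvre.
- A reader might add the quality-of-life tests. They are secondary and lie outside the main conclusion.
- A reader might say that no hypothesis is defined at all. The contrast, a difference in means between independent groups, is defined; the variable is missing.
- A reader might conclude that peak VO2 must lead because entry requires a low value. An entry criterion need not be the outcome, and the design sentence and the respiratory source cited for the effect size point the other way.

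**Conclusion.** The point holds in this form: two domains and nine measures serve the main objective, none is primary, and the sample size fits exactly one between-arm test of a variable that is never named. If all nine are compared between arms at 5% and any one may support the main conclusion, the false-positive risk is about 13% to 28% for common correlations of 0.9 to 0.5, and at most 37%. The correlations are assumptions. Even at 0.9 the risk is about 2.6 times nominal, and only near-perfect correlation (0.95) brings it down to about 10%.

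The article does not establish which variable should lead. Nor does it show that d = 0.8 suits any particular one: Section 2.4 itself opens with "Since no information has been found on the magnitude of the effect on the topic studied".

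**What to change.** Before any outcome data are compared between arms:

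1. Name one primary variable and its contrast: between arms, at the post-program test. The choice is the investigators'. FVC % predicted would fit the design sentence and the respiratory basis of the effect size; peak VO2 % predicted would fit the entry criterion in Section 2.1.1.
2. Test the leading variable of the other domain second, in fixed sequence, each at 5%.
3. Report all other indices, quality of life and within-group changes with 95% confidence intervals, as secondary and without confirmatory claims.
4. State in Section 2.4 which variable d = 0.8 refers to, and that the value is an assumption for that variable.
5. Align the design sentence in Section 2 with the main objectives.
6. State that the between-arm test answers the second main objective. The first, whether the program improves function, rests on descriptive within-arm change, because both arms receive a program.

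**Cost.** Protocol wording, and fewer outcomes that can carry a confirmatory claim. The 26 per group stands as long as d = 0.8 is kept as the assumption for the chosen variable; if the investigators judge a smaller effect realistic, the number has to be recalculated. Keeping all nine as primary under Bonferroni would instead need 43 per group.

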## 3. Discussion

There is growing evidence that postoperative patients with CHD should engage in physical exercise training. However, CRPs in pediatric populations remain significantly underutilized, and clinical research into this promising form of intervention is notably sparse. Currently, there is no standardized framework for designing such programs or a clear understanding of their outcomes; only a limited number of clinical trials have investigated the optimal exercise training regimens or strategies to improve adherence in postoperative CHD patients. It is essential to explore exercise modalities that optimize training effects and enhance the quality of life of these patients [38].

The pediatric CHD population has unique and complex needs, suggesting the potential value of exploring innovative intervention beyond general physical exercise. These may include strategies such as ventilatory function recovery, specific strength training based on neurophysiological principles, and comparative analyses of continuous versus interval aerobic exercise. Further research is needed to tailor interventions to the specific characteristics of this patient group [39].

Interval-based aerobic exercise has proven effective in improving functional capacity in cardiovascular patients. This training modality significantly increases VO_2_ max, reflecting enhanced cardiovascular and pulmonary efficiency and improving exercise tolerance. These benefits are particularly relevant in patients with cardiovascular conditions, as they optimize oxygen consumption, exercise capacity, and overall quality of life. Although the superiority of continuous aerobic interval exercise has been established in adults with cardiovascular diseases [40], there are few studies incorporating interval exercise into CRPs for pediatric CHD patients [29]. The CRP proposed in this study integrates both continuous and interval aerobic exercise, which could serve as a model for future research.

The success of CRPs relies on the collaboration of multidisciplinary healthcare teams with specialized expertise and addressing the high associated costs. Adherence challenges are particularly prevalent in hospital-based CRPs, which is why home-based programs are increasingly favored. These home interventions not only reduce costs but also diminish the burden on families. The challenge remains to demonstrate that the benefits in quality of life and functional outcomes are at least equivalent to those achieved in clinical settings [13,14,15].

Incorporating respiratory physiotherapy into CRPs is logical, given that CHD patients often experience impaired pulmonary function, contributing significantly to morbidity and mortality. These impairments are frequently due to restrictive respiratory patterns resulting from thoracotomies, sternotomies, and ventilatory muscle weakness, which collectively worsen lung function [41]. Exploring the potential of specific respiratory physiotherapy techniques, such as volumetric incentive spirometry and IMT, in conjunction with physical exercise, could strengthen respiratory muscles and address cardio-respiratory dysfunction in this population. Although preliminary studies have begun to evaluate the effects of IMT on lung and exercise capacity in pediatric CHD patients [28,42], research remains limited. We propose expanding CRPs to include targeted interventions for enhancing inspiratory volume, and strengthening ventilatory muscles may have broader implications for improving the health status of pediatric CHD patients. Given the scarcity of research in this area, further investigations are required to establish a foundation for optimizing rehabilitation strategies.

It has been documented that during physical exercise, the muscle groups requiring the highest oxygen demand are the respiratory and locomotor muscles, particularly the serratus anterior and the vastus lateralis of the quadriceps. However, these muscles have not been sufficiently targeted in previous CRP studies [13,16,24,26]. Although diaphragm dysfunction has been identified in CHD patients and is linked to restrictive ventilation disorders and exercise intolerance [43], only a few reports have explored the effects of respiratory interventions in patients with a Fontan circulation [27,28,29,30,42]. To date, no controlled clinical trial has examined the full scope of an exercise training program integrated with a comprehensive respiratory physiotherapy regimen in children with CHDs. This highlights the pressing need to describe and implement a structured CRP based on neurophysiological mechanisms.

The program proposed in this study focuses on identifying the specific muscles that require targeted training, distinguishing it from other published programs. Existing programs often advocate general strengthening exercises, such as using wall pulleys and hand weights, without specifying muscle groups or their selection rationale, or rely on general sports activities or games [44]. We propose emphasizing muscles that improve lung inflation (e.g., serratus anterior, pectoralis major) and enhance cardiac preload, as well as lower extremity muscles that act as venous return pumps; for example, the Bauer system—a network of deep veins in the legs surrounded by muscles that facilitate blood return to the heart during contraction and relaxation—and Lejar’s soleus veins, which are critical for venous return during walking [45]. This contrasts with the focus on upper extremity strengthening, which requires higher ventilatory effort compared to equivalent work performed by the lower limbs [46].

### 3.1. Limitations

The results are subject above all to the type of family from which the patients come, influencing the economic level. At this point, and so that this bias is minimized, we propose in our program to provide families with financial transportation assistance in case of belonging to the in-person group.

Children with CHDs are accompanied by high comorbidity. Changes in the process could mean the loss of some subjects from the study. However, we consider that this limitation is the norm in any complex clinical process such as the one at hand.

Children and adolescents suffering from CHDs have been subjected to numerous surgical interventions, medical consultations, and check-ups that have caused multiple absences in their school life. This could cause a lack of adherence to treatment or possible dropouts, especially during the examination stages.

### 3.2. Ethics and Dissemination

This study is being conducted in compliance with the protocol and the principles outlined in the current version of the Declaration of Helsinki [47]. Approval for this study was obtained from the Committee on Clinical Research Ethics of Galicia (CAEI) (registration number: 2017/567).

All participants will be fully informed about this study’s purpose and will provide written informed consent prior to participation. Participant privacy will be safeguarded, with adherence to applicable data protection regulations, and all published data will maintain participant anonymity. Medical information collected during this study will be treated as confidential and will not be shared with third parties. To ensure privacy, each participant will be assigned a randomly generated identification number. Treatment plans will be personalized, with adjustments made as needed to prioritize patient safety and deliver the most tailored care possible. The risk of therapy-related adverse events is considered minimal.

In the event of serious adverse events during or after this study, the participants will be closely monitored by the study team and physicians in line with standard care protocols. All serious adverse events will be documented and reported to the study’s principal investigator within 24 h.

This study will uphold participants’ rights and protect the confidentiality of their data. Each participant will be assigned a unique trial identification number. Personal information will be securely stored at individual study sites in accordance with the 1988 Data Protection Act and will not be included in the trial database. Personal data will only be retained as long as necessary for the purposes for which it was collected.

## Figures and Tables

**Figure 1 jcm-14-00816-f001:**
[figure not shown]
Frames/screenshots from some of the exercises in the TELEA’s video tutorial showing different exercises to strengthen the muscles involved in the venous return pumps visualized through the platform. (**A**) High knee pointed toe, (**B**) standing cross body toe tap, (**C**) standing leg kickback with overhead reach, (**D**) side kick, (**E**) squat, (**F**) lateral sliding lunge, (**G**) standing calf raise with arm lift, (**H**) side lunge with extended leg, (**I**) quadruped leg extension and flexion.

**Figure 2 jcm-14-00816-f002:**
[figure not shown]
Sequence from supine 90/90 hip and knee position to oblique sitting (following Ontogenic patterns) synchronized with breathing to enhance inspiratory muscles (serratus and pectoralis) in a closed kinetic chain in sync with abdominal muscles. Sequence: (**A**) oblique sitting on right arm, (**B**) supine position, (**C**) oblique sitting on left arm.

## Data Availability

The original contributions presented in the study are included in the article, further inquiries can be directed to the corresponding authors.
